### Measurement and data collection

Data collection is structured to comprehensively assess both the implementation process and program outcomes. Incorporating constructs from SCT and key determinants from the EPIS framework, the approach aligns with the broader goal of the program evaluation across all objectives described above. Quantitative data, which will form the basis for evaluating project outcomes, will be obtained through participant surveys, electronic health records, and study-related documentation. Additionally, to further evaluate the implementation outcomes across all study goals, qualitative data will be collected through exit interviews with healthcare providers participating in the project. These interviews will focus on their experiences, perceptions, and engagement with the implementation of the project components.

UT Health ET and FCC will use their EHRs to assess the number of adult patients who are screened for tobacco use and referred to evidence-based tobacco dependence care (Goal 1); receive SDM for LCS; referred to LCS; complete their first LCS (Goal 2); navigated to diagnostic testing and treatment if diagnosed with cancer (Goal 4). Information about referrals and tobacco treatment engagement from the departments and clinics enrolled in this project will be collected by the Texas Tobacco Quitline and provided monthly to the implementation team as part of a larger, summative report of use. The MD Anderson Quitline reports will be used to collect information on patient enrollment, sessions completed, nicotine replacement therapy provided, and abstinence status at 3 and 6-months post-enrollment (Goal 1).

Study team records will be used to assess the number of providers who participate in education on evidence-based tobacco cessation interventions and education about SDM for LCS (Goals 1, 2). Using data from study-related records, we will also evaluate the number of community events in which we interactively provide information to community members and the number of community organizations to receive information about the program. We will also assess the number of healthcare systems and clinics to receive the step-by-step implementation and sustainment guide and hands-on technical assistance and resources to support self-led implementation of the program (Goal 3).

Pre-implementation surveys will be administered to the leadership of UT Health ET participating departments and FCC clinics to profile the providers and characterize the patient population. It will include measures such as the Organizational Readiness for Implementing Change (ORIC) measure [66] and the Lung Cancer Screening-12 (LCS-12) measure to evaluate participants’ knowledge and beliefs related to LCS [67]. To further evaluate the implementation outcomes for all aims, virtual post-implementation surveys will be administered to healthcare providers to assess acceptability of the program and solicit suggestions to improve efficiency and sustainability. Exit interviews with healthcare providers will be completed to assess the acceptability of the program and elicit feedback on the project’s impact on the clinical workflow and staff roles, as well as influential contextual factors (e.g., organizational culture).

### Data analysis

Quantitative outcomes will be assessed with descriptive statistics, frequencies, simple pre- to post-difference tests. Descriptive statistics will summarize clinic demographics, and the people and professionals reached and served. Non-parametric tests will be used to account for the small sample size of clinics whenever only clinic-level data are available. Wilcoxon signed rank sum tests and McNemar’s/Fisher’s exact tests will be used for clinic-level repeated continuous outcomes and categorical outcomes, respectively. The significance level will be set at *p*< 0.05. Data from all quantitative sources will be imported into a SAS file for data management. We will collect and analyze data beyond the objectives listed, including, for example, clinic moderators of change (as power may allow) to inform future work, with attention to collinearity, influential observations, robust standard errors adjusted for clustering within clinics (via mixed effect model), and adjustment for multiple comparisons, and effect size (Cohen’s d). Moderators of care delivery from our prior work include clinic size, clinic readiness to change, and provider smoking status [45, 68].

Qualitative data will be coded inductively with themes drawn from the data. Coding discrepancies will be discussed and reconciled within the team until consensus is reached, refining codes until a final coding frame is agreed upon and reapplied to all transcripts. Coding and analysis will proceed iteratively across each stage of data collection. Constant comparison of data will be used to refine themes, avoid redundancy, ensure fittingness of themes, and check accurate accounting of the dataset. Quantitative and qualitative data will be analyzed separately and merged at the end. Various types of integration will be used to merge the quantitative and qualitative data (e.g., creating a joint table).

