### Organizational and healthcare provider participants

This project involves researchers from The University of Texas MD Anderson Cancer Center (MDACC) and the University of Houston (UH). MDACC, an NCI-designated comprehensive cancer center, is the recipient of funding for this work and houses the MD Anderson Quitline and the Decision Science Core that will be leveraged for the project. The subcontract to UH supports the evaluation expert for this project.

The participating health services organizations are the UT Health East Texas (UT Health ET) and Family Circle of Care (FCC). UT Health ET is the largest healthcare provider in Northeast Texas with over 300 providers in more than 30 specialties who provide care across 50 clinics. Providers in the Departments of Family Medicine, Internal Medicine, and Pulmonary Medicine at UT Health ET will participate in program implementation. UT Health ET houses a Lung Nodule Program, which provides comprehensive LCS, evaluation, and guideline-based treatment of lung nodules. The program uses nurse navigators to facilitate LCS completion, LDCT imaging results reporting, as well as navigating patients with abnormal results to diagnostic testing and surveillance, and to treatment for patients with a lung cancer diagnosis. UT Health ET’s work on this project is supported via a subcontract, which includes funding to support our collaborators from the pulmonary clinic of UT Health ET, a MD who specializes in the treatment of lung disease and lung cancer screening and his lead nurse navigator. The subcontract also includes support for a clinical research coordinator and a nurse navigator for this project. FCC is an FQHC that includes six community-based clinics serving Tyler (4 clinics), Athens (1 clinic), and Jacksonville (1 clinic), Texas. FCC’s participating units include Family Medicine (embedded in 5 clinics), Obstetrics & Gynecology (4 clinics), and Internal Medicine (1 clinic). FCC is also a residency training site for the Department of Internal Medicine at UT Health ET.

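### For clinic-level moderators of change, the plan names cluster-robust standard errors on few clinics without clinic-level degrees of freedom, so false positives can exceed 5% (minor: exploratory analysis)

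*Protocol article*

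**What the plan says.** All of the relevant analysis text is in the Data analysis section of the protocol article.

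- Small-sample safeguard: "Non-parametric tests will be used to account for the small sample size of clinics whenever only clinic-level data are available".
- Threshold: "The significance level will be set at *p*< 0.05".
- Variance method for the additional analyses, which include moderators of change: "robust standard errors adjusted for clustering within clinics (via mixed effect model". The article names no small-sample correction, degrees of freedom, reference distribution or random-effects structure.
- Candidate moderators: "Moderators of care delivery from our prior work include clinic size, clinic readiness to change, and provider smoking status". The first two are properties of a clinic. The third is a property of a provider.
- Status: these analyses go beyond the listed objectives, depend on power, are meant to guide later work, and are to be adjusted for multiple comparisons.

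The number of clinics analysed is not given. Under Organizational and healthcare provider participants, "FCC is an FQHC that includes six community-based clinics". UT Health East Texas as a whole has "over 300 providers in more than 30 specialties who provide care across 50 clinics", but only three departments take part: "Providers in the Departments of Family Medicine, Internal Medicine, and Pulmonary Medicine at UT Health ET will participate in program implementation". The number of clinics in those departments is not stated. The total is therefore 6 plus an unknown number, and at most 56.

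**The concern.** The plan recognises that clinics are few and protects the simple clinic-level tests for that reason. It states no such protection for the models used once finer data exist. For a moderator that takes one value per clinic, the information comes from the number of clinics, however many patients each contributes.

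A cluster-robust (sandwich) variance is justified for many clusters. With few, it is biased downward and a normal reference is too narrow. The article's phrase could also mean the model-based error of a mixed model. If that model has only a random intercept, it ignores the possibility that clinics change by different amounts, and the error is again too small.

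At stake is whether clinic characteristics reported as moderators are real. They are meant to guide later work, and the project also sends an implementation guide to other health systems.

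**Working it through.** The article states no power, sample size or expected moderator effect, so there is no figure of its own to reproduce. The check is the true type I error at a nominal two-sided 5% (the sidedness is my assumption).

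**Inputs from the article:** threshold 0.05; 6 Family Circle of Care clinics; an unstated share of a 50-clinic system; ceiling 6 + 50 = 56. Nine clinics would be 6 + 3 if each UT Health East Texas department counted as one unit, which is an assumption.

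**Assumptions not in the article:** m = 30 or 80 patients per clinic and period; baseline rate p = 0.40; between-clinic SD of change τ = 0, 0.2 or 0.35 (logit); equal clinic sizes; no true moderator effect.

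**Set-up.** Let d_j be clinic j's change, x_j its moderator value, G the number of clinics and S = Σ(x_j − x̄)². With equal clinic sizes, the moderator-by-period estimate is b = Σ(x_j − x̄)d_j / S. Its true variance is (τ² + v)/S, with v = 2/[m p(1 − p)].

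**Reading 1: uncorrected sandwich.** The estimated variance is Σ(x_j − x̄)² e_j² / S², where e_j is the residual. The expected e_j² is (τ² + v)(1 − h_j), with h_j = 1/G + (x_j − x̄)²/S. The shortfall is therefore largest in the clinics that carry most weight. Simulation with normally distributed changes and moderator (40,000 runs per row) gave these rejection rates:

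| Clinics | Sandwich, normal | Sandwich, t on G − 1 | Clinic-level regression, t on G − 2 |
|---|---|---|---|
| 6 | 28.5% | 18.8% | 4.9% |
| 9 | 19.9% | 14.5% | 5.0% |
| 15 | 13.9% | 11.3% | 5.4% |
| 30 | 9.3% | 8.1% | 5.1% |
| 56 | 7.2% | 6.6% | 5.0% |

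Simulations with binomial patient data gave the same picture: 29%, 20%, 13 to 14% and 7% for 6, 9, 15 and 56 clinics with a normal reference. A skewed moderator, as clinic size may well be, is worse. With an exponential x_j the normal-reference rates were 30.0%, 22.9%, 16.8%, 11.8% and 9.4% down the rows.

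**Reading 2: model-based error, random intercept only.** This model estimates the variance as v/S and omits τ². With a normal reference, the true error is 2[1 − Φ(1.96 √(v/(v + τ²)))].

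- m = 80: v = 2/(80 × 0.24) = 0.104. For τ = 0.35, v/(v + τ²) = 0.104/(0.104 + 0.1225) = 0.460 and 1.96 × √0.460 = 1.33, giving 18.4%. For τ = 0.2 the result is 9.6%.
- m = 30: v = 2/(30 × 0.24) = 0.278. For τ = 0.35 the result is 10.3%; for τ = 0.2 it is 6.7%.
- τ = 0: 5.0% for either m.

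G does not appear in this formula, so more clinics do not help under this reading.

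**Provider-level moderator.** A separate simulation used a random-intercept model with 10 observations per clinic, intraclass correlation 0.05, 15% prevalence and the uncorrected sandwich with a normal reference. It gave 18% at 6 clinics, 12% at 9, 8% at 20 and 6% at 56. Provider smoking status is thus affected less.

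**The case against.** The strongest reply is that the estimator under criticism is partly assumed. The article does not say that the errors are uncorrected, and its parenthesis allows a mixed model whose random effects carry the clustering. That is correct, and it is why the result is given separately for each reading. A mixed model is not safe by itself, however. Model-based errors gave 5 to 7% at 6 to 9 clinics in a model with a moderator but no period term. The article speaks of moderators of change, and there a random intercept alone can reach 18%.

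A second reply is that degrees of freedom for an exploratory model normally belong in the analysis plan. This has force and keeps the point minor. But the article does name the variance method and ties its small-sample safeguard to a different situation, so an analysis plan that follows it literally would inherit the problem.

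A third reply is that the analysis depends on power and will be adjusted for multiplicity. Both are true. Neither repairs a standard error that is too small: the first concerns missed effects, and the second works on p-values that are already wrong.

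A reader might infer that the plan will reject true nulls several times too often. The documents do not support that. The number of clinics is unknown, the multiple falls to about 1.4 at 56 clinics (7.2/5), and the model-based reading can be at the nominal level.

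**Conclusion.** The point holds in conditional form and is minor. For clinic size and clinic readiness, the named method can exceed its nominal 5%, and the article states nothing that prevents this.

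- Uncorrected sandwich errors, normal reference: about 20 to 30% with 6 to 9 clinics, 13 to 14% with 15, and 7 to 9% with 30 to 56; somewhat higher for a skewed moderator.
- Random-intercept model-based errors: about 5% to 18%, governed by how much clinics differ in change and by patients per clinic.

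These figures rest on the assumed patient numbers, baseline rate and between-clinic SD, and on a range for the number of clinics. None of the evaluation objectives in Table 3 depends on this analysis, so the project's main conclusions are unaffected.

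**What to change.** Add one sentence to the Data analysis section: for moderators measured at clinic level, inference uses clinic-level degrees of freedom. Then name one of the following.

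1. Regress each clinic's change on the moderator, with a t reference on the number of clinics minus the number of parameters. This is the simplest option and held about 5% in every setting checked.
2. Fit a mixed model with a random clinic-by-period effect and Kenward-Roger degrees of freedom.
3. Use bias-corrected cluster-robust errors (CR2 or CR3) with Satterthwaite degrees of freedom.

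Scaling the sandwich variance by G/(G − 1) with t on G − 2 is not enough. In the simulation without a period term it still gave 8 to 17% for clinic-level moderators at 6 to 9 clinics. It would also help to state the number of participating UT Health East Texas clinics, since that determines whether these models are worth fitting.

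The cost is wider intervals and fewer significant moderators. No data collection changes.

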## Discussion

In this protocol, we present a prevention-focused program aimed at increasing rates of tobacco cessation care provision and LCS completion by addressing both needs through a multifaceted, hybrid LCS delivery approach. The project aims to ensure consistent access to evidence-based tobacco screening and cessation care to all adult patients, emphasizing tobacco cessation as the main strategy of lung cancer prevention. For individuals meeting LCS eligibility, the program integrates SDM in participating clinics by training providers to facilitate informed decisions about LCS; this approach ensures better access and uptake of initial LCS and is more responsive to local needs and resources of these healthcare systems and their patients. For LCS completion, the program leverages the benefits of an existing Lung Nodule Program, which provides care and coordination for all aspects of LCS, ensuring consistent quality of care. Additionally, the project prioritizes community engagement to raise awareness about LCS across communities in Northeast Texas by actively disseminating the program to non-participating healthcare systems and clinics to broaden its reach.

The EPIS framework is used to guide the implementation and streamline the integration of SDM for LCS and tobacco cessation interventions in healthcare and community settings and ensure its sustainability by leveraging theory-informed and evidence-based implementation strategies and approaches. The aim of this applied approach is to use best practices of implementation science to ensure that evidence-based tobacco cessation and LCS interventions are integrated into routine clinical workflows of clinics participating in the project. Through these efforts, we seek to improve access to comprehensive lung cancer prevention and early detection services for populations in areas of Northeast Texas through creating a sustainable hybrid model of LCS delivery.

Potential limitations of this community-based LCS program include its generalizability and the feasibility of broader implementation. While we aim to tailor the program to the needs and capacities of participating partner organizations, it may not be directly transferable to other community settings with different resources, infrastructure, and patient populations. Though the current project includes significant implementation support with tailored training, technical assistance, and audit and feedback, it also incorporates a component of community dissemination, where other organizations are encouraged to adapt the program without ongoing support from the project team. These organizations that participate in a self-led implementation might experience additional barriers, such as a lack of training and dissemination materials tailored to their settings and patient populations, limited capacity, and competing demands, impacting the quality of program delivery and its outcomes. However, this project will seek to minimize these barriers by developing a more sustainable model of integrating LCS support into community healthcare systems, which will include an adaptable intervention and flexible implementation model leveraging available community resources.

## Data Availability

The datasets used and/or analyzed during the current study are available from the corresponding author on reasonable request.

## Abbreviations

CMS: Centers for Medicare & Medicaid Services
EHR: Electronic health record
EPIS: Exploration, Preparation, Implementation and Sustainment
ERIC: Expert Recommendations for Implementing Change
FCC: Family Circle of Care
FQHC: Federally Qualified Health Center
LDCT: Low-dose computed tomography
LCS: Lung cancer screening
MDACC: The University of Texas MD Anderson Cancer Center
SCT: Social Cognitive Theory
SDM: Shared decision making
UH: University of Houston
UT Health ET: UT Health East Texas
